#### Secondary outcomes measures

The quality of care perceived by the GP will be measured using a validated set of basic quality indicators [23,24]. Quality Indicators define the degree to which the provided care is in accordance with the evidence-based guidelines. They are usually calculated as percentages based on patient data registered in the electronic medical record and from completed questionnaires. Additionally, the Primary Care Assessment Tool provider survey (PCAT) will be used in a semi-structured interview to measure the quality of care from the perspective of the GP as well. The PCAT provides information on structure and process elements of primary care. This also includes information on patient-, provider-, and facility-related perspectives on the experiences of care received and care provided [25].

The health status of the patient will be assessed by the Short Form 12 (SF-12). This is a multi-purpose generic health status questionnaire, including 12 items scoring on a physical and a mental health scale.

Diabetes control will be measured by means of the glycated haemoglobin level (HbA1c). The HbA1c indicates the glucose control over the past 2-3 months and will be measured at baseline and after 12 months.

Health care utilization will be measured by the number of visits patients make to different health care professionals and changes in the medication lists. This information will be collected through a patient questionnaire which was previously used in the second Dutch National Survey of General Practice [26], adapted from the Health Questionnaire of Statistics Netherlands [27]. The questions include involvement of all relevant health care provided. Changes in the medication lists will be measured by comparing the patients' medication lists at the beginning and end of the intervention period.

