**Methods/Design:**

The study is a randomized controlled trial among patients with T2DM and at least one comorbid chronic disease (N = 230), who already participate in a diabetes management program. Randomization will take place at the level of the patients in general practices. Trained practice nurses (case managers) will apply a case management program in addition to the diabetes management program. The case management intervention is based on the Guided Care model and includes six elements; assessing health care needs, planning care, create access to other care providers and community resources, monitoring, coordinating care and recording of all relevant information. Patients in the control group will continue their participation in the diabetes management program and receive care-as-usual from their general practitioner and other care providers.

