**Discussion:**

We expect that the case management program, which includes better structured care based on scientific evidence and adjusted to the patients' needs and priorities, will improve the quality of care coordination from both the patients' and caregivers' perspective and will result in less consumption of health care services.

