### Objective

The objective of this study is to establish the additional value of case management superposed on a diabetes management program, in terms of perceived quality of care, quality of care from the perspective of the GP, the health status of the patient, diabetes control, and health care utilization in T2DM patients with comorbidity.

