### Randomization

Patients will be randomly assigned to the intervention or control group (*see *Figure 1). Patients in the control group will receive care from the DCS, their GP and PN. Patients in the intervention group will receive the case management intervention from the case manager in addition. All eligible patients in the participating practices will be invited to join the study. Reasons for non participation will be carefully registered.

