**Secondary outcomes**				
b. quality of care perceived by GP	Quality Indicators			X
c. health status of the patient	SF-12	X	X	X
d. diabetes control	Hba1c (%)	X	X	X
e. health care utilization	Contacts with care providers	X	X	X
	Medication use (RAI-CHA)	X		X

**Feasibility**	Semi-structured interviews			X

This table provides an overview of the time schedule of all measurements and measures.

CQ-Index for GP care: Consumer Quality Index for GP care; GP: General Practitioner; HbA1c: glycated haemoglobin level; PACIC: Patient Assessment of Chronic Illness Care; RAI-CHA: Resident Assessment Instrument - Community Health Assessment; SF-12: Short-Form 12.

To get more insight into the factors favoring and hampering the implementation of the case management program, we will perform a feasibility check using semi-structured in-depth interviews and collect data via patient questionnaires.

We will interview four groups: 1) all case managers delivering the intervention, 2) the GPs in the participating practices, 3) the diabetes nurses of the DCS, as well as 4) a random stratified selection of 15 patients of the intervention group (both patients who indicated in their questionnaire having been exposed well and poorly to the case management program). The interviews will be recorded using a voice recorder.

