### Outcome assessment

Primary and secondary outcome measurements are assessed at baseline, at 3 and 12 months. Interim analyses will be carried out three months after the baseline measurement. This analysis will be purely descriptive concerning changes in the quality of the received care according to the patient as a result of participation in the case management program.

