The case managers work together with the PN and GP to discuss the results from the initial assessment and during the design of the care plan before it is presented to the patient. During this contact the GP and PN might get motivated to use specific elements in the usual care group, who do not receive the intervention. This could lead to contamination. However, the GP and PN are not involved in the program (the actual problem assessment with the patients, the monthly monitoring, the contacts between the case manager and participant) and therefore we expect this form of contamination, if it occurs, will be washed out in a short period and will not influence the intervention effect after 12 months.

This study started in October 2009 by designing the program and making all practical arrangements for the start and implementation of the intervention. In February 2011 the first patients were included in the study. Follow-up of patients will continue until July 2012.

The results of this study will become available at the beginning of 2013.

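### The PCAT interview with GPs who treat both arms cannot estimate the randomised effect, and the protocol contradicts itself on when the GP-perspective outcome is measured

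*Protocol article*

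**What the plan says.** All references are to the protocol article.

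- **Objective.** The added value of case management is to be judged on several outcomes, one of which is "quality of care from the perspective of the GP". The abstract's Discussion expects that the programme "will improve the quality of care coordination from both the patients' and caregivers' perspective"; the main Discussion repeats this.
- **Instruments (Secondary outcomes measures).** Two are listed. The first is a set of quality indicators that express how far care follows the guidelines. They are usually percentages worked out from patient records and completed questionnaires. The second is the PCAT provider survey, which "will be used in a semi-structured interview to measure the quality of care from the perspective of the GP as well". It is said to describe how primary care is structured and carried out.
- **Unit of randomisation (abstract, Methods/Design).** "Randomization will take place at the level of the patients in general practices".
- **Who treats the control arm (Randomization).** "Patients in the control group will receive care from the DCS, their GP and PN".
- **Schedule, first statement (Outcome assessment).** "Primary and secondary outcome measurements are assessed at baseline, at 3 and 12 months".
- **Schedule, second statement (Table 2).** The row "quality of care perceived by GP" lists Quality Indicators with a single mark, at 12 months. The PCAT does not appear. Semi-structured interviews appear once, under Feasibility, at 12 months.

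**The concern.** An instrument can estimate the effect of a randomised intervention only if its values can be attached to a randomised arm. Here the patient is randomised, but the PCAT respondent is a GP whose patients fall in both arms. If the survey is reported as a secondary outcome, readers may take it as evidence on whether case management improved care as the GP sees it. As described, it cannot supply that evidence.

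The indicators can, but the article does not settle whether they have a baseline value. If Table 2 is followed, the trial gives up precision on a named objective, although much of the source data already sits in the medical record when patients enter.

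The label adds to the difficulty. The indicators measure agreement with guidelines from patient data, which is not the GP's perception. The PCAT is therefore the only instrument here that records the GP's own view, and it is the one that cannot be split by arm.

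**Working it through.** The article gives no figure for this outcome, so the main check compares unit, instrument and timing.

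**1. Can the PCAT be split by arm?**
- Randomised unit: the patient, within practices.
- Control patients are cared for by their own GP and practice nurse.
- The same GP helps draw up the care plans of intervention patients. The main Discussion recognises the overlap as a contamination risk: "During this contact the GP and PN might get motivated to use specific elements in the usual care group".
- The GPs to be interviewed are those of the participating practices (text below Table 2). They are not identified by arm, and their number is not given.
- No question about one arm's patients, or about individual patients, is described.

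A GP-level answer from a GP with patients in both arms has no arm label. The between-arm contrast is therefore undefined on what is described.

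**2. Can the indicators be split by arm?** Yes. They are built from patient data and each patient has an arm. Randomisation makes a 12-month comparison valid without a baseline.

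**3. Timing, side by side.**

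| Source | Quality indicators | PCAT |
|---|---|---|
| Outcome assessment section | baseline, 3 and 12 months | baseline, 3 and 12 months, if it counts as a secondary outcome |
| Table 2 | 12 months only | no row; 12 months only if it belongs to the Feasibility interviews |

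Both statements cannot hold for the indicators.

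**4. Size of what the indicators can show.** The plan's sample size, set for the primary outcome, reproduces: 2 × (0.75 × (1.960 + 0.842) / 0.3)² = 98.1 per arm against 98 stated, and 98 / 0.85 = 115.3 against 115 recruited.

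Take 98 patients per arm, one measurement at 12 months, a two-sided 5% test and 80% power. Assume that every patient counts in the indicator's denominator. The control percentages below are also assumptions.

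| Assumed control percentage | Detectable difference (percentage points) |
|---|---|
| 50% | 19.6 |
| 60% | 18.4 |
| 70% | 16.5 |
| 80% | 13.5 |

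So a comparison by arm is available, but only for fairly large differences.

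**5. What a baseline would add.** Under linear adjustment for a baseline value with correlation r, the variance of the arm difference falls by about r², and the detectable difference is multiplied by about √(1 − r²). The values of r are assumed.

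| r | Variance saved | Multiplier | 19.6 points becomes | 13.5 points becomes |
|---|---|---|---|---|
| 0.3 | 9% | 0.954 | 18.7 | 12.9 |
| 0.5 | 25% | 0.866 | 17.0 | 11.7 |
| 0.6 | 36% | 0.800 | 15.7 | 10.8 |

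For a yes/no indicator these are approximations.

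**The case against.** The strongest reply is that the objective already has a usable instrument. The quality indicators are named first, are the only entry in Table 2 for this outcome, and can be compared by arm. The PCAT is described as an addition, and a descriptive provider interview beside a trial is legitimate. No between-arm PCAT analysis is stated, and the expected caregiver benefit is not tied to it. Covariates may be left to an analysis plan that is not shown. The sentence under Outcome assessment may also be a loose summary, since Table 2 gives medication use no 3-month mark either.

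Most of this stands, and it rules out several stronger readings that a reader might infer:

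- *That the GP-perspective objective cannot yield any between-arm comparison.* The indicators can be compared by arm, validly, at 12 months.
- *That the PCAT contrast is zero by construction.* It is undefined as described. The scoring rests on a cited source that is not at hand, and an interview could be worded to ask about each arm's patients, although nothing of the kind is described.
- *That no before-after contrast exists.* One section promises a baseline, records could be read back to earlier dates, and the PCAT's 12-month timing is only inferred from the Feasibility row.
- *That the indicators will be analysed without baseline adjustment.* The Analyses section lists no covariates for them either way.

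The reply does not remove two things. The PCAT stands among the secondary outcome measures although its answers, as described, cannot be assigned to an arm. And if Table 2 governs, the indicators have no scheduled baseline; if the text governs, Table 2 is wrong.

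**Conclusion.** The point holds in a limited form. As described, the PCAT interview cannot estimate the randomised effect, and it is missing from Table 2. This rests on two readings of the article: that participating GPs have patients in both arms, and that no arm-specific rating is collected. The indicators can carry the between-arm comparison, but the article contradicts itself on when they are measured.

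The loss from a 12-month-only comparison is one of precision, not of validity: about 9% to 36% of the variance for assumed correlations of 0.3 to 0.6. The documents give no correlation and no indicator rates, so this range is illustrative. The matter concerns one secondary outcome and a headline expectation. It is worth correcting because the correction is cheap and an arm label that was not collected cannot be recovered in the analysis.

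**What to change.** 1. Reconcile the Outcome assessment section with Table 2. Add a baseline mark for the record-based quality indicators, and reword the general sentence so that it names the outcomes measured at each time.
2. Compare the indicators by randomised arm at 12 months, adjusted for the baseline value.
3. Label them as guideline-concordant care rather than quality perceived by the GP.
4. Report the PCAT interview descriptively, with the feasibility interviews, and show it there in Table 2.
5. Do not present the expected benefit from the caregivers' perspective as a between-arm effect on the strength of the PCAT.

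The cost is a change of wording, an edit to Table 2 and one extra record extraction for baseline, with no new visits. Indicators that depend on questionnaires may not be recoverable for a past date. Those would stay as 12-month comparisons without baseline adjustment, which remain valid.

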### Sample size

The required sample size for this study is calculated on the basis of the main outcome measure, the 'tailored care' subscale of the CQ-Index. Previous research showed mean baseline scores of 3.1 (SD 1.0) on a 5-point scale [20]. We expect a mean improvement of 0.4 in the intervention group and 0.1 in the control group (mean difference in improvement 0.3). Assuming a pooled SD of change of 0.75 (SMD = 0.40), we would need complete data for 98 patients in each group; given 80% power and a significance level of 5%. We will recruit 2 × 115 patients allowing a drop-out rate of 15% during follow-up.

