### Analyses

The effectiveness of case management will be established in multivariate multilevel analyses, according to the intention-to-treat principle. When possible, specific attention will be paid to identify subgroups of patients characterized by their profile of comorbidity in which the intervention is more effective than in other subgroups. The data might allow calculating an individual case management exposure level score, in the intervention group as well as in the control group. This will enable analyses of the outcome measures according to the per-protocol principle. Differences between patients exposed to the case management program and patients in the control condition on patient's health care utility and patient's health status will be tested using a chi-square test and student t-test, respectively. Potential confounding is checked, including the effect of different case managers and the number of patients per case manager.

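### The primary effect is framed and sized as a change score, and SF-12 is given a plain t-test, although baseline is collected; committing to baseline adjustment would cost nothing and could add power

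*Protocol article*

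**What the plan says.** The Sample size section of the protocol article is the only place where the primary effect is given a numerical form. It expects gains of 0.4 and 0.1 in the two arms, hence "mean difference in improvement 0.3", and continues: "Assuming a pooled SD of change of 0.75 (SMD = 0.40), we would need complete data for 98 patients in each group". The power is 80% at a 5% level. The source for spread is given as "Previous research showed mean baseline scores of 3.1 (SD 1.0) on a 5-point scale". Recruitment follows as "We will recruit 2 × 115 patients allowing a drop-out rate of 15% during follow-up".

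The Outcome assessment section states "Primary and secondary outcome measurements are assessed at baseline, at 3 and 12 months", and Table 2 marks a baseline value for CQ-Index, PACIC, SF-12 and HbA1c.

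The Analyses section says that effectiveness "will be established in multivariate multilevel analyses, according to the intention-to-treat principle". It does not say whether the modelled outcome is the 12-month score or the change, and it does not name the baseline score as a covariate. Potential confounding is to be checked. For health status it names a Student t-test.

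**The concern.** A change score subtracts the whole baseline value, which fixes the baseline coefficient at 1. A model with baseline as covariate estimates that coefficient. The change score is fully efficient only when the regression slope of the 12-month score on baseline, r × SD(12 months)/SD(baseline), equals 1. When the slope differs from 1, the change score has a larger residual variance and remains sensitive to chance baseline imbalance. A t-test on SF-12 carries no covariate, whether it is applied to 12-month scores or to changes.

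What is at stake is precision already paid for. The baseline questionnaires are in the schedule, and the sample size has no slack: 115 × 0.85 = 97.75 completers against a requirement of 98, with no allowance for clustering.

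**Working it through.** **Inputs (Sample size section).** Difference 0.3; SD of change 0.75; baseline SD 1.0; 98 complete patients per group; 80% power; 5% level. Sidedness is not stated; the two-sided formula reproduces the 98, whereas one-sided would give 78.

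**Step 1: reproduce the plan's figure.**
- n per group = 2(1.960 + 0.842)² / (0.3/0.75)² = 15.70/0.16 = 98.1. This is 98 as stated, or 99 if rounded up.
- Standard error at 98 per group = 0.75 × √(2/98) = 0.75/7 = 0.107, so 0.3/0.107 = 2.80 and power is 80.0% (79.6% by noncentral t).

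**Step 2: implied correlation.** The 12-month SD is not given. *Assume* it equals the baseline SD of 1.0.
- SD of change² = 2 × SD² × (1 − r), so r = 1 − 0.75²/2 = 0.719.

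**Step 3: baseline-adjusted analysis.**
- Residual SD = 1.0 × √(1 − 0.719²) = 0.695.
- Variance ratio to the change score = 0.695²/0.75² = 0.86, or 14% less variance.
- Power at 98 per group: 0.3/(0.695/7) = 3.02, giving 85.6% (85.2% by noncentral t).
- For 80% power, about 85 complete patients per group would do by the normal approximation.

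**Step 4: relax the equal-SD assumption.** Hold baseline SD at 1.0 and SD of change at 0.75, and let s be the 12-month SD. Then r = (1 + s² − 0.5625)/(2s) and residual SD = s√(1 − r²). Power is by the normal approximation at 98 per group.

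| s | r | residual SD | power |
|---|---|---|---|
| 0.9 | 0.693 | 0.649 | 89.9% |
| 1.0 | 0.719 | 0.695 | 85.6% |
| 1.1 | 0.749 | 0.729 | 82.1% |
| 1.25 | 0.800 | 0.750 | 80.0% |

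In the last row the slope is 0.8 × 1.25 = 1, so the change score and the adjusted analysis coincide.

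**Step 5: vary the common SD.** The SD of 1.0 is quoted for a 5-point scale, while the Primary outcome measures section describes the tailored care items as scored on 4 points. Keeping SD of change at 0.75 and equal SDs at both times, a common SD of 0.75 gives 89.9% and one of 1.2 gives 83.8%.

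Like the plan's own calculation, none of these figures allows for clustering by practice or case manager.

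**The case against.** The strongest reply is that the article never commits to analysing change scores. That wording sits in the sample-size paragraph; the Analyses section specifies a multilevel model and leaves room for a baseline covariate. Sizing on an SD of change and then adjusting for baseline is legitimate and usually conservative. A condensed article may also leave covariates to a fuller document. All of this stands, and an omitted covariate alone would not be a finding. What remains is what the article does state: its only definition of the primary effect is a difference in change, and it names a covariate-free test for an outcome measured at baseline. Even the second item has a limit. The t-test sentence follows the remarks on exposure scores and per-protocol analysis, and may be meant for that comparison only.

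A reader might also infer that power collapses if the true correlation is lower, say 0.5. The documents do not support this as a criticism. The SD of change of 0.75 is stated directly; with equal SDs of 1.0, a correlation of 0.5 replaces it with 1.0, and no section suggests that value. It is a hypothetical only.

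Finally, 85% does not follow from the plan's figures alone. It needs the 12-month SD, which the plan does not give; hence the range above.

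**Conclusion.** The point holds as a modest matter of efficiency and pre-specification. The 98 per group is not in error, and a reader should not conclude that the trial is undersized on this ground or that baseline adjustment is ruled out. Committing to it would raise power from about 80% to about 85% if the 12-month SD is 1.0. For 12-month SDs between 0.9 and 1.25, with the other two SDs as stated, the gain lies between about 10 points and nil. Apart from one degree of freedom, adjustment does not lose precision. The size of the gain is uncertain because the 12-month SD is not given and because the 5-point and 4-point descriptions leave the baseline SD itself in doubt.

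**What to change.** - In the Analyses section, define the primary estimate as the between-arm difference in 12-month tailored care score from the multilevel model, with the baseline score as covariate.
- Replace the plain t-test for SF-12 with the same baseline-adjusted form, and use it for PACIC and for HbA1c at 12 months. For HbA1c, first reconcile Table 2, which marks a 3-month value, with the Secondary outcomes measures section, which mentions only baseline and 12 months.
- In the Sample size section, state the 12-month SD assumed alongside the SD of change of 0.75 (if 1.0, then r of about 0.72), and settle whether the subscale has 4 or 5 points.

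The cost is a few sentences of wording. No additional data are needed, and the recruitment target can stay as it is.
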